### Statistical analysis

#### Sample size calculation

The sample size calculation is performed using GLIMMPSE32 and based on published data on MASA-C scores [49]. A total sample size of 111 participants (37 per group), is needed to demonstrate a different evolution over time in the experimental groups and the control group at a significance level of 0.05 and a power of 0.8 when using repeated measures with Geisser-Greenhouse correction (3 groups × 4 time points). Based on previous research on prophylactic swallowing exercises by Carnaby-Mann and colleagues [19], we expect a baseline MASA-C score of 195, with a decay in the first 6 weeks to 171 in the control group, 177 in the app group and 180 in the therapist group. After 6 weeks we assume no further decline. A standard deviation of 11 is considered for the MASA-C scores at each time point, this is also based on the standard deviations (SDs) reported in Carnaby-Mann et al. [19]. First-order auto-regressive correlation (AR [1]) is assumed for the covariance structure between the repeated measures, with a base correlation of 0.4 and a decay rate of 0.5. The targeted total sample size, taking into account more than 20% dropouts, is 150 (*n* = 50/group).

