#### Data analysis

Patients will be analyzed in the groups to which they are assigned (intention-to-treat). Descriptive statistics will be used to summarize patient characteristics per treatment group. Data will be analyzed using linear mixed-effects models with group, time and group by time interaction as fixed effects. A random intercept will be added to account for correlation between measurements coming from the same individual. When one or more overall effects are significant, post-hoc pairwise testing with Bonferroni-Holm correction for multiple testing will be performed. Missing data is assumed to be missing at random (MAR) and, thus, will be ignored in the analyses. By using mixed-effects models for the analysis, we can incorporate all information on the available time points. If more than 15% of the data is missing, a sensitivity analysis will be conducted by using multiple imputation. Results of the original analysis of the available cases will be interpreted in the context of sensitivity analysis.

Additionally, the impact of adherence, HPV status, dosimetry and mucositis on the different functional endpoints will be studied in exploratory linear mixed-effects models. Fixed main-effects and interactions with group for all these factors will be evaluated.

More details on the primary, secondary and exploratory analyses can be found in the statistical analysis plan.

A *p* value of less than 0.05 will be considered statistically significant. All analyses will be conducted using SPSS Statistics version 25 (IBM, Chicago, IL, USA) and R software (R Foundation, Auckland, New Zealand).

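### The sample size assumes within-patient correlation that decays over time, but the stated random-intercept model implies constant correlation, so standard errors for change from baseline would be modestly wrong, in both directions

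*Protocol article*

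**What the plan says.** Two neighbouring sections of the protocol article describe within-patient correlation differently.

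- **Sample size calculation.** A first-order autoregressive correlation "is assumed for the covariance structure between the repeated measures, with a base correlation of 0.4 and a decay rate of 0.5". The test that is powered is "repeated measures with Geisser-Greenhouse correction (3 groups × 4 time points"), and the result is: "A total sample size of 111 participants (37 per group), is needed".
- **Data analysis.** A linear mixed model with group, time and their interaction as fixed effects. On within-patient correlation it says: "A random intercept will be added to account for correlation between measurements coming from the same individual". It mentions no serial residual correlation, robust standard error or sphericity correction. Post-hoc pairwise tests follow a significant overall effect, with no time point singled out. Further detail is left to the statistical analysis plan, which is not shown.

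The outcome measures section schedules MASA-C at eight occasions: baseline, four weekly visits, end of CRT, and 1 and 3 months after CRT. The sample size uses four.

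**The concern.** A random intercept with independent residuals gives the same variance at every visit and the same correlation between any two visits. The sample size section assumes that correlation falls as visits move apart. Both cannot hold for the same outcome.

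If the planning assumption is the true one, the model uses an average correlation for every contrast. Visits close together are in fact more strongly correlated than that average, so their change standard errors are too large. Visits far apart are less correlated, so theirs are too small. Intervals for the latest change from baseline would then be too narrow. This bears on the question the trial was sized for, a different evolution over time between groups.

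**Working it through.** **Inputs, all from the sample size section.** Three groups and four time points; alpha 0.05; 37 per group; SD 11 at each time point (variance 121); mean 195 at baseline, then 171, 177 and 180 with no later decline; base correlation 0.4, decay 0.5.

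**Assumption on the correlation.** The article does not give the formula behind the decay rate. I read it as a linear-exponent autoregressive correlation on equally spaced time points:

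- one step apart: 0.4^1 = 0.400
- two steps apart: 0.4^1.25 = 0.318
- three steps apart: 0.4^1.5 = 0.253

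**Step 1: reproduce the stated sample size.**

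- After baseline the group means differ from their average of 176 by −5, +1 and +4. The squares sum to 25 + 1 + 16 = 42.
- With no difference at baseline and the same difference at the three later points, the interaction sum of squares per patient per group is 42 × 3/4 = 31.5.
- The average correlation over the six pairs is (3 × 0.400 + 2 × 0.318 + 0.253)/6 = 0.348, so the within-patient error variance is 121 × (1 − 0.348) = 78.9.
- Noncentrality at 37 per group is 37 × 31.5/78.9 = 14.8, on 6 and 324 degrees of freedom before correction.
- The sphericity epsilon is 0.979. With the Geisser-Greenhouse correction, power at 37 per group is 0.822 by the noncentral-F approximation and 0.808 by simulation (20,000 runs).
- The smallest size reaching 0.80 is 36 per group (108 in total), close to the stated 111.

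A pure AR(1) with correlations 0.4, 0.16 and 0.064 does not reproduce it: it needs 43 per group and gives power 0.737 at 37.

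**Step 2: standard errors under the random-intercept model.** With complete data the model's residual variance estimates the average variance minus the average covariance, 78.9. For a group difference in change from baseline:

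- model SE = sqrt(4 × 78.9/37) = 2.92 at every time point
- true SE = sqrt(4 × 121 × (1 − r)/37), where r is the true correlation with baseline
- actual level of a nominal 5% test = 2 × [1 − Φ(1.96 × model SE/true SE)]

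| Time point | r | True SE | Model/true | Actual level | 95% coverage |
|---|---|---|---|---|---|
| 2nd | 0.400 | 2.80 | 1.042 | 4.1% | 95.9% |
| 3rd | 0.318 | 2.99 | 0.978 | 5.5% | 94.5% |
| 4th | 0.253 | 3.13 | 0.934 | 6.7% | 93.3% |

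**Step 3: the overall group-by-time test.** With complete balanced data the random-intercept interaction test equals the uncorrected repeated-measures F test. Its simulated type I error under the planning correlation is 5.0% to 5.3%. Spreading the same decay over eight occasions gives 5.3% to 5.4%, and the baseline-to-last coverage stays at 93.3%.

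**Step 4: group contrasts at one visit.** With SD 11 throughout, the SE is sqrt(2 × 121/37) = 2.56 whatever the correlation between visits, so these contrasts are unaffected.

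**Step 5: sensitivity to a steeper decay.** Pure AR(1) 0.4 is an assumption that does not reproduce 111. Average correlation is (3 × 0.4 + 2 × 0.16 + 0.064)/6 = 0.264. The SE ratios are 1.108, 0.936 and 0.887, so tests run at 3.0%, 6.7% and 8.2%. The overall test runs at about 5.7% with four visits and about 6.7% with eight equally spaced visits.

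**Step 6: power if the covariance matches the planning assumption.** Treating the covariance as known, power at 37 per group is 0.804. Neither 111 nor 150 needs to change.

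**The case against.** The strongest reply is that the planned test barely notices the mismatch. The trial is powered for the group-by-time test; under the plan's own correlation that test holds its level, and power is about 0.80 to 0.82 with or without the sphericity correction. This stands.

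It also stands that the article names no key contrast. Baseline to 3 months is a reasonable contrast to examine, but a reader who infers that the trial's main comparison is invalid goes beyond the text. Pairwise group comparisons at one visit are an equally natural reading of the post-hoc tests, and those are unaffected under equal SDs.

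A reader might treat the missing Geisser-Greenhouse correction as an error in itself. It is not: that correction belongs to univariate repeated-measures analysis of variance. The issue is the restrictive covariance.

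A reader might also infer much larger error rates, around 10% for the overall test. Those need visit-to-visit correlations of 0.7 to 0.8, which the article does not state. The 8.2% in step 5 likewise rests on a decay that does not yield 111.

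Finally, the sentence says that a random intercept is added; it does not rule out a serial residual structure, and the analysis plan may supply one. That limits how firmly the point can be put. But the article presents the random intercept as the means of handling within-patient correlation, and on its own it contradicts the planning assumption. If the analysis plan does add a structure, this sentence should say so.

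**Conclusion.** The inconsistency is real and modest in size. If correlation decays as planned, the random-intercept model misstates SEs for group differences in change from baseline by +4%, −2% and −7% at the second, third and fourth time points. The last is the unfavourable one. The overall test remains near its nominal level, and the sample size is sound.

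These figures rest on the linear-exponent reading of the decay rate, equal spacing, complete data, equal SDs and no residual structure beyond the random intercept. If the true correlation were constant, there would be no error; if it fell more steeply than planned, the error would be larger. The documents do not support an unconditional claim that the trial's error bars are wrong.

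**What to change.** In the data analysis section, replace the random-intercept covariance with an unstructured within-patient covariance, fitted by REML with Satterthwaite or Kenward-Roger degrees of freedom. State in advance the order of fallbacks if it does not converge: for example heterogeneous Toeplitz, then a random intercept plus serial correlation in actual time. Use the same rule for the strength and QOL outcomes.

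The change is one of wording and needs no extra patients. An unstructured matrix has 4 × 5/2 = 10 parameters if four visits are modelled and 8 × 9/2 = 36 if all eight are. With more than 20% dropout allowed for, the eight-visit version carries some risk of non-convergence, which is why the fallback order should be fixed beforehand.

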### Patient and public involvement

Pre-recruitment there has been a try-out with a small number of patients. They were questioned about the feasibility of the exercise protocol. Also, during the study all participants are asked about their experiences regarding the exercises. In the context of the application, all patients are questioned about their familiarity with smartphones, tablets and computers. Before the start of the study, the application has been tested by a number of people from different age groups.

## Discussion

An increasing number of studies have shown a significantly positive effect of PSE on swallowing function in HNC patients treated with CRT. However, low adherence rates are a major issue, preventing clinical implementation of PSE. There is an internationally recognized need to develop the most efficient PSE protocol in which the adherence rates are maximized. This multicenter randomized trial will investigate the effect of adherence-improving measures on actual patient compliance, swallowing function, muscle strength and QOL. It is expected that this study will result in an optimized, patient-supported and evidence-based PSE program improving patient compliance.

## Data Availability

The datasets generated during the current study are not publicly available since they will contain patient data and the informed consent does not include sharing-data publicly. The datasets are available from the corresponding author on reasonable request. All clinical record forms will be collected and managed using REDCap (Research Electronic Data Capture) electronic data capture tools hosted at Ghent University Hospital [58].

## Abbreviations

1RM: 1 repetition maximum
AR (1): First-order auto-regressive correlation
CCRT: Concomitant chemoradiotherapy
CRT: (Chemo)radiotherapy
CTAR: Chin-tuck against resistance
HNC: Head-and-neck cancer
HPV: Human papillomavirus
IOPI: Iowa Oral Performance Instrument
MAR: Missing at random
MASA-C: Mann Assessment of Swallowing Ability–Cancer
MIP_a_: Anterior maximal isometric pressure
MIP_p_: Posterior maximal isometric pressure
PSE: Prophylactic swallowing exercises
QOL: Quality of life
RCT: Randomized controlled trial
REDCap: Research Electronic Data Capture
SEA: Swallowing exercise aid
SLP: Speech and language pathologist
TSE: Tongue-strengthening exercises
